### 2.1. Venue

The intervention programme takes place in five different natural environments in the countryside (Table 1). They are not located far from urban areas, but participants in a previous pilot study have experienced that they are completely surrounded by natural environments [64,65].

Every second time the group meets during the 12-week course, they meet up at their base camp to create a safe base for the group processes. The base camp is located close to a nature school and consists of a fireplace and a shelter. Every other time, the group meets in a new nature environment with different qualities in the southern part of Funen.

The nature environments are selected with inspiration from the Perceived Sensory Dimensions (PSD): serene nature rich in species and refuge, which are identified as most important to people with symptoms of stress [16,66,67]. The five local nature environments (see Table 1) have been selected during the pilot project [64,65]. They are based on feedback and preferences from former participants. The former pilot study shows that the participants have preferences for different types of nature; therefore, shore, forest, tunnel valley, hill, and meadowland are represented as settings in the ‘Wildman Programme’. These natural environments are carefully selected but not unusual or exceptional; rather, they represent a spectrum of natural environments in Denmark. The nature environments are also selected so that the participants easily can access them by private or public transport and the environments are easy for the participants to visit alone or with their families after the course has ended.

### 2.2. Participants

Inclusion criteria: The participants are men, aged 18–76 years old, living in the region of southern Funen in Denmark. The male participants are on long-term sick-leave and suffer from stress (ICD: F43.8 and F43.9), anxiety (ICD: F41.2), or depression (ICD: F32.0) according to the ICD, the International Classification of Diseases [68]. Moreover, the participants can suffer from diseases such as chronic cancer, post-cancer, chronic obstructive pulmonary disease (COPD), cardiovascular disease, or type 2 diabetes—all of which can cause stress. We expect that the nature-based ‘Wildman Programme’ can help men with a wide variety of chronic illnesses improve their quality of life and reduce symptoms of stress. Many of the participating men included in the study will in the beginning of the course to some extend experience lower quality of life and not have benefitted sufficiently from participation in other available rehabilitation interventions.

The participants will be divided into groups of 10–18 individuals in the ‘Wildman Programme’. Approximately 40% of the participants will be recruited from the health centre in the Municipality of Svendborg and the Municipality of Faaborg-Midtfyn, approximately 40% will be recruited from the jobcentre in the Municipality of Svendborg and the Municipality of Faaborg-Midtfyn, and the remaining 20% will be recruited from the general practitioners. The control group will be recruited as a form of a natural experiment from comparable departments in the health centre and the job centre and from other general practitioners.

The study will include at least 104 participants: 52 in the intervention group and 52 in the control group. The diagnoses, ages, job status, and social status of the participants will be recorded. Instead of selecting participants to be included in the intervention group and TAU by randomisation, we have chosen to follow two groups via a type of natural experiment or quasi-experiment. We choose to select the TAU group from matched health centres, job centres, and general practitioners via their normal standard routines, where the groups are matched with respect to age, gender, and diagnosis [69]. The matched control group (*N* = 52) of men will resemble the men in the intervention group with regard to the distribution of age, job status, and levels of stress to ensure that the participants in the intervention and control group are as similar as possible (see Figure 2).

The participants in the control group receive traditional treatment and rehabilitation in the healthcare system of the municipalities, which do not take place in nature. They participate in physiotherapeutic treatment, fitness training, mindfulness courses, and traditional rehabilitation programmes (consisting of e.g., physical exercise, nutritional counselling, and education about their illness).

The exclusion criteria are psychosis or psychotic disorders, brain injuries, addiction or physical disabilities that prevent them from participating in the physical exercise programme or move about in nature.

### 2.3. Intervention

The ‘Wildman Programme’ is led by a nature guide and a health professional (e.g., a physiotherapist, a nurse, or a psychologist) who are experienced in rehabilitation of the included diagnosis and further educated in the nature-based rehabilitation methods. Based on past experiences in the ‘Wildman Programme’, the drop-out rate is expected to be approximately 15% due to the participants’ return to work, hospitalisation, or because the intervention does not suit them.

The intervention has a duration of 12 weeks with one weekly three-hour meeting [24]. In addition, the participants are given homework such as breathing exercises and meditation techniques for around 15 min a day, and they should give themselves breaks during the week by spending time in a self-selected supportive environment in nature in their home area. There are 10–18 participating men in each group of the ‘Wildman Programme’.

The intervention has a permanent chronological structure, which is the same every time the intervention groups meet, but the intervention elements are adjusted accordingly to seasons and weather conditions.

The ‘Wildman Programme’ is described as a ‘Nature–Body–Mind–Community’ (NBMC) approach focusing on nature experiences, body awareness training, attention training, and supporting community spirit explored in the group at base camp and in five other nature environments with different nature qualities.

The NBMC approach has been developed in a pilot project during the period 2014–2018 [64,65]. The ‘Wildman Programme’ consists of the following main elements: (1) Nature environments and nature experiences, (2) Body awareness, (3) Mind relaxation and meditation, and (4) Fire talks, storytelling, and community spirit. In nature, the participants in the ‘Wildman Programme’ will experience bonfires, storytelling, meditation, breathing exercises, and sensory perceptions to reconnect with nature. They listen to the birds, the wind, and the sounds of the creek, and they feel the soil and the leaves and bark on the trees. They lay on their back on the ground, looking up in the treetops, seeing the shades and colours of light and the motion made by the wind; they lie totally quiet and just are in soft fascination [16,32,70,71].

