### 2.4. Nature Environments and Nature Experiences

In the ‘Wildman Programme’, the participants will be introduced to different nature environments that are expected to have a supportive effect. The environments are selected based on nature qualities that according to the Perceived Sensory Dimensions (PSD) can make the participants feel comfortable and inspire to inner peace which, according to SET, can reduce stress [16,27]. Nature environments and nature experiences belong first and foremost to the sphere “nature” in SET.

The participants will also be supported to sense and restore their contact with nature. In the programme, they will regularly be trained in enhancing their sensory perception of nature [59,72]. Experiencing nature alternately through different senses are expected to help them be more present and forget about negative thoughts in the moment, since they are focusing on the aesthetics of nature [28,39,59,73].

In the ‘Wildman Programme’, the participants are also presented with biological knowledge and stories about nature and our evolutionary relationship with nature, which also are expected to help them move from their directed attention to soft fascination. Wondrous stories about nature (e.g., selected stories about trees, plants, animals, or other natural phenomena) can make nature more accessible to the participants and ‘open’ nature to the men in the ‘Wildman Programme’ [74]. The ‘Wildman Programme’ will take place all year round and in all kinds of weather, which gives the participants the opportunity to reconnect with the cycles of nature, the seasonal changes, and the powers of nature.

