#### 2.4.1. Body Awareness

Many of the men participating in the ‘Wildman Programme’ will have little body awareness and experience problems with their balance. Therefore, in the ‘Wildman Programme’, the participants will be introduced to balance exercises and body and stretching exercises inspired by research on Qigong [48].

Calligraphy health Qigong is an approach that is easy for the participants to engage in and can easily be adapted to the different physical needs in the group and the different nature environments. Qigong exercises are expected to help the participants experience a flow of energy in the whole body and strengthen their body tone and body awareness. In addition, the ‘Wildman Programme’ includes different kinds of outdoor play. These can help the participants strengthen both their physical and mental health, since they increase their heart rate and get their blood circulation activated, while at the same time, they get to play and laugh together [75].

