### 2.5. Outcomes

The participants all experience symptoms of stress and reduced quality of life due to their physical or mental health problems. Therefore, the following outcomes have been selected. All primary and secondary outcomes are measured at baseline (T1), post-treatment (T2), and at follow up 6 months post-intervention (T3).

Primary outcome:

The primary outcome is to investigate whether the results from the NBMC approach in the ‘Wildman Programme’ have a significant effect on the participants’ quality of life. The effect will be measured by the following scale:

Self-experienced quality of life: the World Health Organization (WHO)’s brief questionnaire, WHOQOL-BREF [80].

Secondary outcomes:

The secondary outcomes are to investigate whether the ‘Wildman Programme’ has a significant effect on the participants’ level of stress, self-experienced restitution, and job status. The effects will be measured by the following methods:Level of stress: Cohen’s Perceived Stress Scale (PSS) [81].Self-experienced restitution: The Perceived Restorativeness Scale-11 (PRS-11) [82].Job status: Measured by self-reported job status before, post, and 6 months after the intervention.

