## 3. Research Design

### 3.1. Flow of Participants

The referred men will be invited to an introductory interview before they can be included in the ‘Wildman Programme’. The sample size in the study will be 104 in total: 52 men will be included in the intervention group and 52 men in the control group will be given treatment as usual (see Figure 2).

The strategy to achieve adequate participants in the study is to establish close cooperation with the health centres and job centres in the two municipalities, which have decided to hire a project leader to coordinate the recruitment to the intervention and control group.

The participants in the intervention group and the control group will be answering a questionnaire at baseline (T1), post-treatment (T2), and at follow up 6 months post-intervention (T3).

The questionnaire will include the following scales:Self-experienced quality of life: WHO’s brief questionnaire, WHOQOL-BREF, which examines four domains in a five-point Likert scale: physical health, mental health, social relationships, and health-related environments, for instance access to medical care. The global quality of life is based on the participants’ scores on the four domains, and they range from 0 to 100, with a high score indicating a high quality of life [80].Level of stress: Cohen’s Perceived Stress Scale, PSS, examines the way you handle stress in daily living on 14 items in a five-point Likert scale [81].Self-experienced restitution: The Perceived Restorativeness Scale-11 (PRS-11) [82] measures with 11 items four different categories of self-experienced restitution related to spontaneous attention: fascination, being away, coherence, and scope. The scale is used for measuring meditation practice and attention training in natural environments.Job status: Measured by self-reported job status before, post, and 6 months after the intervention.

Participants from the intervention group and control group will be contacted by e-mail or by phone if they have not answered the questionnaires. No outcome data will be collected on participants that drop out of the study.

No other nature-based interventions are permitted during the trial.

Data will be securely stored in a locked electronic folder at the University, and data will be analysed in SPSS.

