### 4.2. Closure

If this study shows positive effects and significantly can improve life quality and reduce stress among men with stress, anxiety, depression, post-cancer and chronic cancer, COPD, cardiovascular disease, or diabetes type II, the ‘Wildman Programme’ has a potential to be implemented as a rehabilitation programme for men in municipalities in Denmark. Pilot projects prior to this study indicate that the NBMC approach used in the ‘Wildman Programme’ can also have beneficial effects on groups of women, groups consisting of both men and women, and on groups of young people. In a future perspective, it would be interesting to investigate the effect of the programme and the methods on new target groups.

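### Men who leave are not followed, though hospitalisation is an expected reason, and no listed outcome identifies such an event, so implementation would be judged on benefit alone

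*Protocol article*

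**What the plan says.** All references are to the protocol article.

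- **Expected drop-out (Section 2.3).** From past courses, about 15% are expected to leave, "due to the participants’ return to work, hospitalisation, or because the intervention does not suit them". No breakdown by reason is given. Section 3.2 uses the same 15%, by the six-month follow-up, in the sample size.
- **Follow-up of leavers (Section 3.1).** "No outcome data will be collected on participants that drop out of the study". Men who merely fail to answer a questionnaire are to be contacted by e-mail or phone.
- **Outcomes (Section 2.5).** The primary outcome is "Self-experienced quality of life: the World Health Organization (WHO)’s brief questionnaire, WHOQOL-BREF". The secondary outcomes are "level of stress, self-experienced restitution, and job status". Section 3.1 lists the same four for the questionnaire at T1, T2 and T3.
- **Analysis (Section 3.2).** Intention-to-treat, linear mixed-effects models, and maximum likelihood for missing data.
- **Setting and population.** The programme "will take place all year round and in all kinds of weather" (Section 2.4). It includes outdoor play, described as useful "since they increase their heart rate and get their blood circulation activated" (Section 2.4.1). Men up to 76 years may enter, including men with COPD, cardiovascular disease or cancer (Section 2.2).
- **Conclusion foreseen (Section 4.2).** If quality of life improves and stress falls, the programme "has a potential to be implemented as a rehabilitation programme for men in municipalities in Denmark".

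**The concern.** The plan names hospitalisation as an expected route out of the study and, by a separate stated rule, ends outcome collection for anyone who takes that route. None of the four outcomes would identify the event. The one condition attached to implementation is benefit on quality of life and stress.

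Two things are at stake. First, the trial could not say how often programme men were admitted, injured or died, nor set that beside usual care, yet the groups named for possible roll-out include men with serious physical illness. Second, a success (return to work) and a serious event (hospitalisation) are merged into one missing value. That also sits poorly with the intention-to-treat analysis in Section 3.2, which calls for outcomes in every man regardless of whether he stays in the programme.

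**Working it through.** **Inputs.** 52 men per arm (Section 2.2); 15% drop-out (Sections 2.3 and 3.2); d = 0.60, 5% significance, 80% power (Section 3.2); SD 18.0 (Section 3.2).

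**1. The plan's own figure.** A two-sided two-sample t-test with d = 0.60 needs 45 per arm. Adding 15% gives 45 × 1.15 = 51.75, so 52 per arm and 104 in total, as stated. (Dividing instead, 45 / 0.85 = 52.9, gives 53 per arm and 106.) So the 15% is built into the sample size as loss to be absorbed.

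**2. Men without later data.** 0.15 × 52 = 7.8, about 8 programme men, leaving about 44. If the same rate applies to controls, about 16 of 104 overall.

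**3. How many could leave through hospitalisation.** The share is not given, so the whole range is shown for 8 leavers:

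| Hospitalised among 8 leavers (assumed) | Proportion of 52 |
|---|---|
| 0 | 0% |
| 2 | 3.8% |
| 4 | 7.7% |
| 8 | 15.4% |

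Every row would look the same in the planned data: about 8 men with no scores after leaving.

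**4. What recording would allow.** If events were recorded in all 52 men and none occurred, the one-sided 95% upper limit for the risk would be 1 − 0.05^(1/52) = 5.6%. With only the 44 who stay it would be 1 − 0.05^(1/44) = 6.6%, and that limit would say nothing about the men who left. With no event outcome at all, neither limit can be stated.

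**5. Direction of bias in the efficacy estimate.** Suppose men who stay gain 0.60 × 18 = 10.8 points (assumption). The mean over all programme men is 0.85 × 10.8 + 0.15 × (change in leavers):

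- leavers change by 0: 9.18 + 0 = 9.2
- leavers change by −10.8: 9.18 − 1.62 = 7.6
- leavers gain 21.6, for instance because many returned to work: 9.18 + 3.24 = 12.4

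The mean in those who stay can therefore be too high or too low. The mixed model keeps the T1 scores of leavers, and T2 scores of men who leave later. It corrects only for the part of their course that those earlier scores predict.

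**The case against.** **The article condenses a fuller protocol.** Adverse-event procedures may stand there, and their absence from an article would be no finding by itself. That is right. What remains is stated text: the rule in Section 3.1, the explicit outcome list in Section 2.5 and the benefit-only condition in Section 4.2.

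**The rule bars outcome data, not every record.** Also right. Reasons for leaving were evidently known in past courses and may be noted again. But nothing in the article says that they, or admissions, will be recorded and reported by arm.

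**A reader might infer that no outcome captures harm.** The text does not support this. WHOQOL-BREF covers physical and mental health and PSS covers stress. Both can worsen, and both are compared with usual care. The limit is that they do so only in men who still answer, and that a score does not identify an admission or a fall.

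**A reader might infer that the programme's likeliest harms are being removed from view.** This is not supported either. Hospitalisation is one of three reasons, is not linked to the programme, and may reflect the underlying cancer, COPD or heart disease. The plan also contains safeguards: exclusion of disabling physical conditions (Section 2.2), a health professional as co-leader and activities adjusted to weather (Section 2.3), and an introductory interview (Section 3.1). Controls exercise too (Section 2.2). The uncertainty over cause is a reason to record events in both arms, since one arm alone cannot separate disease from programme.

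**Section 4.2 speaks of potential only.** True. It is hedged discussion text, not a recommendation or a decision rule, so only a qualifying clause is needed there.

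**Conclusion.** The point holds as a gap in what the trial could conclude about safety. About 8 of 52 programme men are expected to leave, between 0 and 8 of them through hospitalisation. Under the rule as written these men give no later outcome data, and no listed outcome would identify the event in either arm. Implementation potential would then rest on benefit alone.

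This assumes that a man who leaves the programme counts as having dropped out of the study, which the shared 15% in Sections 2.3 and 3.2 suggests but does not settle. It also assumes that no separate safety recording exists in a document not shown. If it does, the remedy shrinks to stating that it covers both arms and continues after a man leaves.

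The article supports neither a claim that the programme causes admissions nor a claim that the efficacy estimate is biased in its favour. The conflict between ending collection at drop-out and analysing by intention-to-treat stands in any case.

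**What to change.** 1. **Section 3.1:** replace the drop-out rule so that men who leave the programme or usual care are still followed to T3 where they agree.
2. **Both arms, T1 to T3, including leavers:** record reason for leaving, hospital admission, injury during activity, and death. One questionnaire item and a short leaving form suffice.
3. **Section 2.5:** list these as a descriptive safety outcome, reported as counts and proportions by arm with intervals. Matching on age, gender and diagnosis makes the side-by-side reading sensible, though not proof of cause.
4. **Section 4.2:** add that implementation potential will be judged together with these results.

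The cost is slight added data work and one descriptive table. The counts will be too small for a formal test, and none should be planned. The sample size and the primary analysis model are unchanged.

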### 2.4. Nature Environments and Nature Experiences

In the ‘Wildman Programme’, the participants will be introduced to different nature environments that are expected to have a supportive effect. The environments are selected based on nature qualities that according to the Perceived Sensory Dimensions (PSD) can make the participants feel comfortable and inspire to inner peace which, according to SET, can reduce stress [16,27]. Nature environments and nature experiences belong first and foremost to the sphere “nature” in SET.

The participants will also be supported to sense and restore their contact with nature. In the programme, they will regularly be trained in enhancing their sensory perception of nature [59,72]. Experiencing nature alternately through different senses are expected to help them be more present and forget about negative thoughts in the moment, since they are focusing on the aesthetics of nature [28,39,59,73].

In the ‘Wildman Programme’, the participants are also presented with biological knowledge and stories about nature and our evolutionary relationship with nature, which also are expected to help them move from their directed attention to soft fascination. Wondrous stories about nature (e.g., selected stories about trees, plants, animals, or other natural phenomena) can make nature more accessible to the participants and ‘open’ nature to the men in the ‘Wildman Programme’ [74]. The ‘Wildman Programme’ will take place all year round and in all kinds of weather, which gives the participants the opportunity to reconnect with the cycles of nature, the seasonal changes, and the powers of nature.

